##### Criteria for Discontinuation or Withdrawal of Participants During the Study

The IST progression protocol (Table 2) shall be applied in a standardised manner, with no individualised modifications to the progression. Persistent inability to follow the prescribed protocol, including unresolved mild discomfort, shall be managed by considering the following criteria for discontinuation or withdrawal:Voluntary withdrawal by the participant: Participants may withdraw at any time and for any reason, as informed in the consent, without penalty or impact on the participant’s medical care.Development or worsening of medical conditions: If, based on the medical judgement of the team or staff, a new condition or the worsening of a pre-existing condition contraindicates continuation with the IST or significantly increases the risk, participants may withdraw from the programme.Adverse events (AEs): Occurrence of a Serious Adverse Event (SAE) or persistent/considerable AE related to participation, which, based on the medical judgement of the principal investigator or study doctor, makes it inadvisable to continue. All these occurrences will be recorded and evaluated according to the safety protocol.Non-compliance with protocol:○Failure to complete a minimum of 90% of the sessions, even after considering the extension of the period.○Persistent inability or refusal to perform exercises according to instructions and proper technique, compromising safety or validity, despite supervision and correction.○Failure to complete scheduled assessments within 20 weeks.Significant lifestyle changes or concomitant treatments: Initiation of unrelated intense exercise, drastic unsupervised dietary changes, or medical treatments that significantly interact with outcomes or safety, as assessed by the research team.Failure to engage in follow-up sessions: If the participant becomes unresponsive and does not attend sessions/assessments, despite reasonable attempts at contact, discontinuation will be considered.

The main reason will be documented in all cases of discontinuation or withdrawal. Data collected up to that point will be securely retained and considered for inclusion in statistical analyses (e.g., intention-to-treat), as described in the ‘Statistical Analysis’ section. Participants who discontinue the intervention will be able to continue with scheduled assessments if they wish to do so, provided that this is feasible.

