1.Other Indicators of Sarcopenia and Dynapenia:○Handgrip Strength: Specific measurement variable: Maximal handgrip strength, measured in kilograms (kg) (Jamar Dynamometer). Analysis metric: Absolute change from baseline to week 17. Method of aggregation: Mean and SD. Time point(s): Baseline (week 0) and post-intervention (week 17). Clinical Relevance: A component of the sarcopenia diagnosis and a predictor of functionality and mortality.○Gait Speed: Specific measurement variable: Usual gait speed over a 4 m course, measured in meters/second (m/s) (Newtest Powertimer). Analysis metric: Absolute change from baseline to week 17. Method of aggregation: Mean and SD. Time point(s): Baseline (week 0) and post-intervention (week 17). Clinical Relevance: A measure of physical performance, a component of the sarcopenia diagnosis, and a predictor of adverse outcomes.○MVIC of other muscle groups: Specific measurement variable: MVIC for the peck deck, pull over, lateral shoulder elevation, leg curl, low back, hip abduction and hip adduction, measured in Newtons (N) (CIEX SYSTEM). Analysis metric: Absolute change from baseline to week 17. Method of aggregation: Mean and SD of the change per exercise. Time point(s): Baseline (week 0) and post-intervention (week 17). Clinical Relevance: Assesses the training response across different body regions.○Sarcopenia Status: Specific measurement variable: Diagnostic status of sarcopenia according to EWGSOP2 criteria (based on muscle strength, muscle mass, and physical performance). Analysis metric: Change in the proportion of participants meeting the diagnostic criteria from baseline to week 17. Method of aggregation: Frequencies and percentages. Time point(s): Baseline (week 0) and post-intervention (week 17). Clinical Relevance: Quantifies the overall impact of the intervention on the diagnostic status of the condition.2.Health-Related Quality of Life (HRQoL):○Specific measurement variable: The index score derived from the EQ-5D-5L descriptive system and the Visual Analogue Scale (VAS) score of the same questionnaire. Analysis metric: absolute change from baseline to week 17 for both the index score and the VAS score. Method of aggregation: Mean and SD of the changes. Time point(s): Baseline (week 0) and post-intervention (week 17). Clinical Relevance: Measures the overall self-perceived health and the impact of the intervention on multiple dimensions of participant well-being.3.Applicability of the IST Protocol:○Perceived Safety: Specific measurement variable: Score on a 5-point Likert scale for perceived safety. Analysis metric: Mean score post-intervention. Method of aggregation: Mean and SD. Time point(s): Post-intervention (week 17). Relevance: Assesses the participant’s subjective perception of safety, providing data to test hypothesis H1.○Acceptance/Satisfaction: Specific measurement variable: (1) Adherence rate (% of completed sessions); (2) Score on a 5-point Likert scale for overall satisfaction. Analysis metric: Percentage for adherence; Mean score post-intervention for satisfaction. Method of aggregation: Percentage for adherence; Mean and SD for satisfaction score. Time point(s): Adherence monitored continuously during the intervention (weeks 1–16); Satisfaction assessed post-intervention (week 17). Relevance: Measures the feasibility and appeal of the intervention to participants, providing data to test hypothesis H2.○Perceived Difficulty: Specific measurement variable: Score on a 5-point Likert scale for perceived difficulty. Analysis metric: Mean score post-intervention. Method of aggregation: Mean and SD. Time point(s): Post-intervention (week 17). Relevance: Evaluates the perception of technical simplicity, providing data to test hypothesis H3.○Adverse events: Specific measurement variable: Incidence, type, severity and causality (relationship to IST). Analysis metric: Frequencies and descriptive summary. Method of aggregation: Counts and percentages. Time point(s): Monitored continuously during the intervention period (weeks 1–16). Relevance: Assesses the objective safety profile of the protocol, providing data to test hypothesis H1.

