#### 2.2.3. Post-Intervention Evaluation

A final assessment will be performed one week after completion of the 16-week IST programme (week 17). All baseline measurements (physiological variables, functional capacity including MVIC and posture, quality of life by EQ-5D-5L, and the components of the sarcopenia diagnosis) will be repeated to assess any changes induced by the training, with the exception of the genetic analysis, which is only performed at baseline. Additionally, applicability questionnaires (safety, acceptance and perceived difficulty using Likert scales) [87] will be administered to assess the IST protocol.

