#### 2.3.2. Analysis Strategy

Primary and secondary quantitative variables will be compared pre-post with Student’s *t*-tests for related samples, after testing for normality (Shapiro-Wilk). If the data are not normally distributed or contain outliers, non-parametric tests (e.g., the Wilcoxon signed-rank test) will be employed. Effect sizes (Cohen’s d) and confidence intervals will be calculated. Multivariate analyses will include a multiple linear regression to explore the influence of genetic and environmental variables on strength and muscle mass improvement, with Bonferroni correction for genetic analyses. Qualitative variables (e.g., sarcopenia diagnosis) will be analysed by using McNemar tests. Applicability variables (Likert scales, adverse events) will be analysed with descriptive statistics and *t*-tests or Wilcoxon tests for pre-post comparisons on Likert scales. Additionally, exploratory subgroup analyses will be performed to assess whether the response to IST on primary variables differs according to sex, age ranges (70–79 vs. ≥80 years) and baseline severity of sarcopenia/dynapenia. Adjustment for baseline covariates will be considered in regression models. The software will be IBM SPSS v29.0 and R v4.3.1.

For the assessment of the secondary hypotheses concerning the applicability (Section 2.2.2) of the IST protocol, specific analyses will be carried out:

Hypothesis H1 (low injury risk): This will be assessed through two approaches. First, Adverse Events (AEs) will be recorded (including their type, severity, and causality), and ‘low risk’ will be inferred if the incidence of IST-related injuries is minimal and comparable to or lower than rates reported in the literature for strength training in older adults [1,33,34,35]. Second, Perceived Safety will be measured post-intervention using a 5-point Likert scale; the approach for this subjective scale is based on similar methods used in previous research [87]. The hypothesis will be supported by a mean score of ≥4.

Hypothesis H2 (high acceptance): This will be assessed by: (1) compliance rate, with a success threshold of ≥90% of completed sessions, and (2) a satisfaction score from a 5-point Likert scale administered post-intervention, using a validated measurement approach [88]. The hypothesis will be supported by a mean satisfaction score of ≥4.

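### The applicability scales are given only at week 17, so participants who stop training early are likely to be under-represented in the means that settle H3 and partly settle H1 and H2

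*Protocol article*

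**What the plan says.** Section 2.2.1 of the protocol article gives each of the three 5-point scales a single time point, week 17. The entry for safety reads "Score on a 5-point Likert scale for perceived safety. Analysis metric: Mean score post-intervention" and the entry for difficulty reads "Score on a 5-point Likert scale for perceived difficulty. Analysis metric: Mean score post-intervention". For acceptance, adherence is followed through the programme but satisfaction is asked only afterwards. Section 2.2.3 places the scales in the final visit: "applicability questionnaires (safety, acceptance and perceived difficulty using Likert scales) [87] will be administered to assess the IST protocol". Table 1 agrees.

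Section 2.3.2 turns the means into decision rules. For satisfaction, "The hypothesis will be supported by a mean satisfaction score of ≥4". Perceived safety has the same cut-off and difficulty must average 2 or less. H1 also looks at training-related injuries and H2 also requires at least 90% of sessions. H3 has no second component.

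On people who stop training, Section 2.1.2 says: "Participants who discontinue the intervention will be able to continue with scheduled assessments if they wish to do so, provided that this is feasible". Section 2.1.3 adds that they will be encouraged to attend the week-17 visit where practicable, in order to support the intention-to-treat analysis. At the point of stopping, only the main reason is recorded.

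**The concern.** Whether a participant is present at week 17 is plausibly linked to what the scales measure. Section 2.1.2 applies the progression without individual modification and sends lasting inability to follow it, including mild discomfort that does not resolve, to the discontinuation criteria. Those criteria also cover related adverse events, refusal to perform the exercises and low attendance. A person who leaves for such a reason is more likely than others to give a poor score, and less likely to come back to give it.

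The result would be a mean tilted towards safe, accepted and simple. These are secondary outcomes, but applicability is in the trial's title and is one of its strategic objectives. Section 4 justifies the single-arm design as a feasibility step before a randomised trial, and Section 5 ties clinical uptake to confirmed efficacy and applicability.

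**Working it through.** **Planned losses.** Section 2.3.1 states N = 15 for a paired t-test with d = 0.80, 80% power and two-sided α = 0.05. Exact noncentral-t power is 0.790 at n = 14 and 0.821 at n = 15, so 15 reproduces. Allowing for 15% losses, 15/(1 − 0.15) = 17.6, rounded up to 18. The plan therefore anticipates 18 − 15 = 3 losses.

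**Formula.** Let k of 18 starters have no score, let m be the mean of those assessed, and let s be the score the k people would have given. Then

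all-starter mean = [(18 − k)·m + k·s]/18.

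The documents give no distribution for the scales and no return rate for leavers, so k and s are assumptions and are shown as ranges.

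**Assessed mean exactly at the cut-off, all three losses unassessed (k = 3).**

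| Scale | s | All-starter mean | Assessed mean needed to meet the cut-off over all 18 |
|---|---|---|---|
| Safety, satisfaction (m = 4.0) | 1 | (60 + 3)/18 = 3.50 | (72 − 3)/15 = 4.60 |
| | 2 | (60 + 6)/18 = 3.67 | (72 − 6)/15 = 4.40 |
| | 3 | (60 + 9)/18 = 3.83 | (72 − 9)/15 = 4.20 |
| Difficulty (m = 2.0) | 3 | (30 + 9)/18 = 2.17 | (36 − 9)/15 = 1.80 |
| | 4 | (30 + 12)/18 = 2.33 | (36 − 12)/15 = 1.60 |
| | 5 | (30 + 15)/18 = 2.50 | (36 − 15)/15 = 1.40 |

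The shift at the cut-off is 0.17 to 0.50 points in each direction.

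**Two worked cases.** Fifteen people averaging 4.2 pass the ≥4 rule; with three more at 2 the mean is (63 + 6)/18 = 3.83, which does not. Fifteen averaging 1.8 for difficulty pass the ≤2 rule; with three more at 4 the mean is (27 + 12)/18 = 2.17, which does not.

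**Fewer unassessed leavers.** With k = 1 and the assessed mean at the cut-off, the all-starter mean is 3.83 to 3.94 for safety and satisfaction and 2.06 to 2.17 for difficulty. With k = 0 there is no shift.

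**Missing-data methods.** Section 2.3 says multiple imputation or mixed models under MAR will be considered. The scales have a single scheduled administration, so a mixed model has no repeated measure to use. Section 2.3.2 mentions pre-post comparisons on Likert scales, but no section schedules an earlier administration. Imputation could use attendance, adverse events and the reason for stopping. It could not remove dependence of missingness on the unseen score itself.

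**The case against.** The strongest reply is that the protocol separates stopping training from leaving the study. Leavers may continue assessments, are encouraged to attend week 17, and would complete the scales there. A reader might infer that dissatisfied participants will be largely missing. The documents do not support that: only those who withdraw fully, decline or cannot attend are lost, and no rate is given. What stands is that attendance is optional. Someone who stops in week 3 would be asked about 14 weeks later.

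A reader might also infer that the scales alone decide H1 to H3. That is true only of H3. Adverse events are asked about at every session, so those before stopping are captured. Compliance penalises leaving directly. If three people stop after 6 of 32 sessions (18.75%) and 15 attend everything, mean adherence is (15 × 100 + 3 × 18.75)/18 = 86.5%, below 90%, provided adherence is averaged over all 18. In that case H2 would miss its compliance threshold whatever the satisfaction mean.

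Other reservations stand too. Several listed reasons for stopping, such as new medical conditions or treatments, need not go with poor scores. Section 2.1.2 requires the reason to be documented but does not require a contact, and it foresees unresponsive participants. Contraction time doubles from 45 s to 90 s over the programme (Table 2), so an early score describes a different exposure.

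These replies limit the size of the problem and how completely any remedy can work. They do not supply the scores of leavers who stay away.

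**Conclusion.** The point holds as a risk of favourable selection in secondary outcomes. It is not a defect in the primary analysis and does not show that the applicability results will be wrong. Under-representation is likely because return is voluntary and the reasons for leaving overlap with what the scales measure; its extent cannot be known from the documents.

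If all three planned losses are unassessed and would have scored 1 to 3 (3 to 5 for difficulty), a mean at its cut-off is about 0.2 to 0.5 points too favourable. The scale verdict changes only if those assessed average between 4.0 and about 4.2 to 4.6, or between about 1.4 to 1.8 and 2.0 for difficulty. The exposure is greatest for H3, which has no other component. A cheap change is worthwhile because scores not collected at stopping cannot be recovered later.

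**What to change.** In Table 1 and Sections 2.2.1 and 2.2.3, add that anyone who stops training after at least one session is given the three scales when the reason for stopping is documented, in person or by telephone, where they can be reached. Keep the invitation to week 17.

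In Section 2.3.2, base the H1 to H3 means on everyone who started training, using the stopping score where no week-17 score exists. Report alongside:

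- the number assessed out of all starters;
- the mean from week-17 scores only;
- a sensitivity analysis giving anyone with no score the worst value (1 for safety and satisfaction, 5 for difficulty).

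The cost is three questions for about three people. The primary outcomes stay at week 17. The downside is that stopping and week-17 scores reflect different exposure, which is why the week-17-only mean should be shown, and the means may be slightly less favourable. Unresponsive participants would still have no score; the sensitivity analysis covers them.

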	Continuous monitoring: Record of attendance, protocol compliance, adverse events (see Section 2.4.3), medication and lifestyle changes (see Section 2.1.3).	Weeks 1 to 16
Final Evaluation	(Post-Intervention Evaluation): Repetition of all baseline measurements (except genetic analysis), repetition of sarcopenia diagnostic tests to assess changes; applicability questionnaires (safety, acceptability, difficulty).	Week 17 (one week after the end of the 16-week IST)
Closing of the Study	Final data analysis, preparation of reports and scientific publications.	After Week 17

**Table 2 healthcare-13-01573-t002:** The 16-week IST protocol.

Weeks	Total Working Time	Part 1		Part 2		Part 3	
		Time	%MVIC	Time	%MVIC	Time	%ME
1–4	45″	15″	20	15″	40	15″	100
5–8	60″	20″	22	20″	42	20″	100
9–12	75″	25″	24	25″	44	25″	100
13–16	90″	30″	26	30″	46	30″	100

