##### Adherence to and Compliance with the Protocol

To promote adherence to the protocol and facilitate compliance, the following measures will be implemented:Each participant will attend individually, with a pre-established, adapted timetable.The sessions will be supervised and led by a qualified personal trainer and the principal investigator, who will provide ongoing support and motivation.If a participant misses two or more consecutive excused sessions, the intervention period may be extended by up to four additional weeks to allow time for recovery.

To comply with the protocol, participants must:Complete at least 90% of the scheduled sessions.Carry out all scheduled assessments within 20 weeks.Do not make significant changes in their daily lives that could interfere with the results or safety of the study. Specifically, participants will be instructed:○To maintain their usual dietary habits and not to start any special diets or significant nutritional supplementation without consulting the research team.○To refrain from starting new intense physical exercise programmes or substantially increasing their usual physical activity beyond the IST programme.○Continue with their usual medical care and prescribed treatments, as long as they do not directly interfere with the objectives and safety of the IST (as assessed by the research team). Any relevant new medication or treatment initiated will be recorded (see Section 2.1.3).

Non-compliance with these criteria will be recorded. The criteria for discontinuation or withdrawal from the study are detailed below:

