#### 2.2.2. Pre-Intervention Assessment

One week before starting the 16-week IST, a comprehensive baseline assessment will be performed on the selected subjects to collect baseline data. This assessment, conducted by a physical activity professional and the research group doctor, will allow for detailed monitoring and accurate assessment of the effects of the programme, including the following variables:Physiological Variables: BP and heart rate HR (Omron M3 Comfort^®^ blood pressure monitor, HEM-7134-E, Omron Healthcare Co., Kyoto, Japan) and O2 saturation (OXYM4000 pulse oximeter, Quirumed S.L.U., Valencia, Spain) will be measured. Three resting measurements will be taken per participant, using the mean as the final data.Functional Capacity:○MVIC: The MVIC of each muscle group of the IST programme will be assessed at individualised intermediate angles (determined according to anatomical structure and motor restrictions, recorded with a HALO© digital goniometer). The CIEX SYSTEM machine (Ciex Systems©, Durango, Spain) with sensors and Chronojump software (Chronojump Boscosystems^®^, Barcelona, Spain) will be used for instantaneous measurement and visualisation of strength, tools also used in all IST sessions and for monitoring purposes.○Static Posture Assessment: Participants will be photographed in anatomical position (frontal and sagittal planes) with a Casio Exilim Pro EX-F1 camera (configuration: level tripod, lens at umbilical height, at 4 m, optical zoom, aperture priority, focal length 50 mm, f5.6, ISO 200) [81]. An analysis of documented validity and reliability for postural analysis will be performed with Kinovea^®^ software (v.0.9.x+) [82,83]. Adhesive markers or direct image identification may be used for key anatomical points [84] (sagittal: tragus, C7, acromion, greater trochanter, lateral femoral epicondyle, peroneal malleolus; frontal: acromions, anterior superior iliac spine (ASIS), posterior superior iliac spine (PSIS), patellar centre, tibial malleoli). Postural parameters will be calculated from these points (sagittal: head-neck alignment (HNA) [82], shoulder alignment, estimated spinal curvatures, pelvic tilt [84], knee alignment; frontal: head tilt/symmetry, shoulder height, pelvic symmetry [81], lower limb alignment [82]). Angles (degrees) and distances (cm/mm, after calibration if size reference is used) shall be recorded. Pre-post change will be an outcome of interest. Image analysis shall be performed, if possible, by a blinded assessor (see Section 2.1.3) [83].HRQoL: The EuroQol EQ-5D-5L questionnaire (5 items, 5 dimensions, 5 response levels) will be used [85,86]. This instrument includes two parts: a descriptive system comprising five dimensions (mobility, self-care, usual activities, pain/discomfort, anxiety/depression), each with five response levels, and a VAS where participants rate their overall health.Applicability of the IST Protocol (scales administered post-intervention):○Safety (H1): Assessed by: (1) Analysis of Adverse Events (AEs) (incidence, type, severity, relationship to IST) over 16 weeks (procedures detailed in Section 2.4.3); ‘low risk’ if the incidence of IST injuries is minimal. (2) Perceived Safety: 5-point Likert scale (1 = extremely unsafe, 5 = extremely safe) post-programme, with face validity and based on similar approaches [87]; a mean score ≥ 4 will be expected.○Acceptability (H2): Assessed by compliance rates (≥90% sessions) and overall satisfaction (5-point Likert scale: 1 = extremely dissatisfied, 5 = extremely satisfied) post-programme, using validated measures [88]; a mean satisfaction score ≥ 4 will be expected.○Difficulty (H3): Assessed with a 5-point Likert scale on perceived challenge (1 = not challenging at all, 5 = extremely challenging) post-programme, validated approach [89]; a mean score ≤ 2 will be expected.Genetic Analysis: Saliva samples will be collected using buccal swabs (4N6FLOQSwab, Life Technologies, Waltham, MA, USA). DNA will be extracted from these samples (QIAmp DNA Mini kit, Qiagen, Venlo, The Netherlands) and subsequently quantified (Qubit, Life Technologies). Genetic polymorphisms, specifically Single Nucleotide Polymorphisms (SNPs) and Insertions/Deletions (INDELs), will be analysed in genes associated with the response to strength training, hypertrophy, and strength gains [63,64,65,66,67,68,69,71,72,73]. Specifically, genes linked to the following will be analysed:○Muscle fibre typology: such as ACTN3 (R variant associated with a higher proportion of type II fibres, crucial for strength/power and affected by sarcopenia/dynapenia in ageing) [63,64].○Response to training: including ACE [63,65,66], NRF2, CKMM, MCT1, AMPD1, and the co-activators PPARGC1A and PPARGC1B (involved in mitochondrial biogenesis and exercise adaptation).○Muscle fibre damage and regeneration: genes such as IGF2, MLCK, CASP [72], MMP3 [72], TNC and GDF5 [73], which influence the response to exercise microtrauma and its repair. Moderate exercise-induced muscle damage (EIMD), potentially triggered by IST at long angles, is considered to contribute to remodelling and adaptation.○Vascularisation: NOS3 and VEGFA [67,69], essential for oxygen/nutrient supply, muscle growth and recovery, optimising metabolic stress and hypertrophic response.○Inflammation: TNF-α, CRP [60], IL-6 [60] and IL6-R, which are relevant because inflammation contributes to sarcopenia and modulates the anabolic response [70].○Oxidative damage response capacity: SOD2 [71], CAT and GPX, crucial for muscle recovery and adaptation to training stress.○Fat and carbohydrate metabolism (nutrigenomic factors): Polymorphisms in FABP2, ADRB2, ADRB3, FAT/CD36, UCP2, GCKR, ADCY5 and GIPR, which may influence nutrient uptake and hypertrophic response [74,75,76].

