#### 2.4.3. Collection, Assessment, Reporting and Management of Adverse Events (AEs)

Active safety monitoring will be performed throughout the study.

Collection: In each training session, the trainer will actively ask about unusual complaints or symptoms (requested AEs). Participants will be instructed to spontaneously report any AEs between sessions to the principal investigator or trainer. All AEs will be systematically recorded.Assessment: The description, dates, intensity (mild, moderate, severe), seriousness (if Serious Adverse Event—SAE), measures taken and causality (relationship to SAE) of each AE will be documented by the principal investigator and the study doctor. A SAE will be defined as one that results in death, is life-threatening, requires hospitalisation/prolongation of life, results in significant disability/incapacity, or is a congenital anomaly.Reporting: All AEs will be recorded in each participant’s CRF. AEs will be reported to the Research Ethics Committee of the University of Deusto according to its regulations and deadlines.Management: Care will be provided in the event of an AE. If the AE is mild and related to the intervention, a temporary break may be considered (although progression is standardised). If the AE is moderate, severe, or considered a SAE, or if deemed necessary for participant safety by the principal investigator or study doctor, discontinuation of the participant’s involvement will be considered (as detailed in Section 2.1.2). Any participant who suffers harm as a result of trial participation will receive appropriate medical treatment.

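### The adverse-event outcome behind H1 is fixed to weeks 1–16, which conflicts with study-long monitoring and leaves events from the week-0 and week-17 maximal tests outside the defined count

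*Protocol article*

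**What the plan says.** Three places in the protocol article give the AE outcome a 16-week window:

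- Section 2.2.1, secondary outcomes, adverse events: "Monitored continuously during the intervention period (weeks 1–16"), given there as evidence for H1.
- Section 2.2.2, safety assessment for H1: "Analysis of Adverse Events (AEs) (incidence, type, severity, relationship to IST) over 16 weeks (procedures detailed in Section 2.4.3").
- Table 1 (Section 2.1): "Continuous monitoring: Record of attendance, protocol compliance, adverse events (see Section 2.4.3"), with weeks 1 to 16 in the timing column.

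Section 2.4.3 sets a wider period: "Active safety monitoring will be performed throughout the study". Its collection procedure is narrower: "In each training session, the trainer will actively ask about unusual complaints or symptoms (requested AEs"). Participants are also told to report events themselves between sessions, and all AEs are to be recorded.

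The MVIC of all eight muscle groups is tested at week 0, one week before training starts, and again at week 17, one week after it ends (Table 1, Sections 2.2.2 and 2.2.3). Section 2.1.2 adds that after missed sessions "the intervention period may be extended by up to four additional weeks to allow time for recovery".

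Section 2.3.2 judges H1 partly on whether IST-related injuries are few and no more frequent than published rates for strength training in older people. It gives no time window of its own.

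**The concern.** The article states two periods for the same safety information and does not say which one defines the outcome. Because the H1 rule in Section 2.3.2 is silent on timing, the 16-week wording in Sections 2.2.1 and 2.2.2 governs the count.

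Taken as written, that wording leaves out two maximal-effort occasions on the same machine. One is the week-0 test, the first maximal effort on it that the article describes. It also leaves out complaints that appear after the last session, which follows the block with the longest contractions (90 s in weeks 13–16, Table 2).

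Two things are at stake. One is ascertainment: whether anyone asks about these events. The other is definition: whether an event that is known enters the H1 summary. In a sample of 18, a judgement that injuries are minimal can turn on a single participant.

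**Working it through.** **1. The plan's own figure, used here only as the denominator.** Section 2.3.1: paired t-test, d = 0.80, two-sided α = 0.05, 80% power. Exact noncentral-t power is 0.790 at n = 14 and 0.821 at n = 15, so N = 15. Allowing for 15% losses, 15 / 0.85 = 17.6, rounded up to 18. The figure reproduces, and nothing in this point changes it.

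**2. Calendar.** The stated window is weeks 1–16, or 16 weeks. Study procedures run from week 0 to week 17, or 18 weeks. Coverage is 16/18 = 89%. This is a share of time, not of risk.

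**3. Where an event arises, and what the text does with it.**

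| Origin of the event | Within weeks 1–16? | Actively asked about (Section 2.4.3)? | In the H1 count as written? |
|---|---|---|---|
| Week-0 MVIC test | No | Not at that visit; a persisting complaint may surface at the first session | No, if dated by onset |
| Training, weeks 1–16 | Yes | Yes, at each session | Yes |
| After week 16, between last session and final assessment | No | No | No |
| Week-17 MVIC test | No | No | No |
| Extension session | Depends on the reading | Yes, at each session | Unclear |

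Two cases add to the ascertainment gap. A participant hurt at week 0 who never starts training never meets the session question. A participant who stops training but returns for the final assessment, as Sections 2.1.2 and 2.1.3 allow, has no scheduled questioning in between.

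**4. Size of the extension ambiguity.** Scheduled sessions: 16 × 2 = 32. Extension: up to 4 × 2 = 8 sessions. If week 16 were a hard cut-off, at most 8/32 = 25% of a participant's sessions would fall outside it. The number would be smaller if the 20-week limit on assessments binds. If the window moves with the extension, the figure is 0%.

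**5. Effect of one omitted participant.** With k of 18 participants counted as injured, the incidence is k/18. Adding one who was left out gives (k + 1)/18. The difference is 1/18 = 0.056, or 5.6 percentage points; for example, 0% becomes 5.6%. It is zero if that participant already has a counted event.

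**6. Link to the H1 verdict.** Section 2.3.2 sets no numeric limit for a minimal incidence and quotes no literature rate. Whether a 5.6-point shift would change the verdict cannot be calculated from the document.

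**The case against.** The case on the other side has four parts.

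*Events outside the window are recorded anyway.* Section 2.4.3 covers the whole study and has all AEs entered in the case report form. Sections 2.2.2 and Table 1 both refer to it, and the research group's doctor takes part in both assessments. This stands. A reader might infer that test-visit injuries will be lost, and the article does not show that. It shows that they are not actively asked about and are not in the defined outcome.

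*The extension is covered.* Section 2.1.2 extends the intervention period itself, which is the period Section 2.2.1 refers to. Adherence carries the same weeks 1–16 label, yet the 90% attendance rule is applied after allowing for the extension. Active questioning happens at every session, which would include added ones. This largely stands. Reading extension sessions as excluded goes too far; the text is ambiguous.

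*Leaving out test injuries is legitimate.* H1 is about training, and MVIC testing is an assessment procedure. This is a fair choice of definition, but the article does not say it is making it, and it would not explain leaving out late complaints caused by training.

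*The direction of bias is unknown.* It is tempting to say the window favours H1. Omission can only lower the trial's own count, but H1 compares that count with published rates. Whether those rates include testing injuries cannot be seen here. If they do not, a training-only count is the like-for-like comparison. This stands, and it is the reason to report the two kinds of event separately.

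**Conclusion.** The inconsistency is real and worth correcting. The H1 safety outcome is limited to 16 weeks in three places, while Section 2.4.3 claims the whole study but describes active questioning only at training sessions. Following the outcome definition literally would leave out injuries from the week-0 and week-17 maximal tests and complaints arising after week 16 but before the final assessment.

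The size is up to 5.6 percentage points per omitted participant. This assumes a participant-level incidence, all 18 in the denominator, and no other counted event in that participant. The document does not support a claim that such events go unrecorded, that extension sessions are definitely excluded, or that the comparison with the literature is biased in a known direction. No sample size, primary outcome or test is affected.

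**What to change.** 1. State one AE window in Sections 2.2.1, 2.2.2 and 2.4.3 and in Table 1. It should run from the start of the week-0 MVIC test to the end of the final assessment and explicitly include any extension.
2. Ask the same AE question at the final assessment, including of participants who stopped training early. Ask about the week-0 test at that visit and again at the first training session.
3. Report test-related and training-related events separately, and say in Section 2.3.2 which of them H1 uses. The training-only rate can then still be set against published rates.

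The cost is a change of wording and one extra question at visits already scheduled. The reported incidence may come out slightly higher.
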